### Data Integrity and Analysis

All collected data will be securely stored on a server hosted at Université Laval, with access restricted to the research team. Data will be retained for 7 years after the study’s completion to support planned publications, after which it will be permanently deleted. Given the low-risk nature of this trial, a Data Monitoring Committee is not required, and no interim analysis will be conducted.

### Statistical Analysis Plan

Descriptive statistics will be used to summarize participants’ characteristics and outcome measures at the different measurement times. Participants who withdraw from the study and the reasons for withdrawal will be analyzed. Any harm or unintended effects will be recorded by both the treating family physician and physiotherapist at the beginning of each consultation, as well as by the participants during the follow-up evaluations on REDCap. If a participant experiences an adverse event, the principal investigator will report it to the Ethics Committee. However, since the interventions included in this trial are commonly used in clinical practice and are generally well tolerated, no major adverse events directly related to the intervention are expected, except perhaps a temporary increase in pain.

For each of the primary and secondary patient-reported outcome measures, repeated measures analyses will be performed using linear mixed models with a random effect by participant to account for the correlation present in repeated measures within individuals. The model allows assessment of the group and time effects, as well as the group-by-time interaction. An intention-to-treat analysis will be used. Gender and type of MSKD will be used to test the interaction between the group effect and the strata in order to test whether the comparison across interventions depends on gender or type of MSKD. Residual analysis will be performed to verify that the assumptions of normality and homoscedasticity are met. If not, the model will be extended to a generalized linear mixed-model framework. Effect sizes will be presented as the standardized differences between treatment groups in the mean weekly improvements over 12 and 24 weeks. Satisfaction will be compared using chi-squared tests, Mann-Whitney tests, or independent *t* tests.

For economic analyses, the total cost of an episode of care will be calculated from the perspectives of the public health service, the participants, and private insurers. ICERs will then be computed from 3 perspectives: the public health service, the participant, and society. The ICERs will be measured as the difference between the mean costs divided by the difference in effectiveness at 24 weeks between the stepped care model and each of the usual care models [95].

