#### Anterior Knee Pain

Inclusion criteria are (1) anterior knee pain during walking, running or going up or down stairs, or during at least two activities among: kneeling, squatting, and resisted knee extension [55] and (2) maximum score of 79/100 on the Knee Outcome Survey Activities of Daily Living Scale (1.5 times the minimally clinically important difference [56], to ensure participants have clinically significant symptoms). Exclusion criteria are (1) history of knee surgery or patellar dislocation, and (2) pain believed to originate either from the meniscus [57] or any knee ligament based on clinical tests.

The primary objective is to assess the equivalence between the stepped care model and the 2 usual care models. With 123 participants per group, we will have 80% power to test the noninferiority of the stepped care model compared to usual rehabilitation care and usual medical care, using a noninferiority margin of 2.0 (out of 10) points on the primary outcome measure. This margin is based on the highest suggested minimally clinically important difference for the Pain Interference subscale of the Brief Pain Inventory—Short Form (BPI-SF) [58]. The sample size calculation assumes a true mean difference of 0 between groups, and an SD of 1.8 in the usual care groups [59], a 15% dropout rate at the 24-week follow-up [20,60-62], and a 1-sided alpha level of .025.

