### Randomization and Blinding

Randomization lists (1:1:1) were generated using a computer-based random number generator by an independent research assistant not involved in the project. Blocked randomization (with random block sizes of 3, 6, and 9) was used to ensure balanced group allocation. Given that randomization was stratified by gender (men, women, and other) and MSKD (low back pain, neck pain, rotator cuff-related shoulder pain, and anterior knee pain), 12 separate lists were generated. The randomization lists were integrated into the REDCap randomization module, eliminating the need for sealed envelopes. After the baseline evaluation, the research associate will enter the participant’s gender and MSKD type into REDCap, which will then generate the assigned group. The allocation will appear in a secure, concealed table within REDCap, preventing any modifications. The research associate will then inform the participant and the medical or physiotherapy clinic of the assigned group to schedule the participant’s first appointment.

Blinding of treatment providers and participants is not feasible due to the nature of the interventions. However, the statistician conducting the analyses will remain blinded to group allocation. Since all study outcomes are self-reported and collected via REDCap, an outcome assessor is not required. Participants will interact with a research associate only at baseline, before randomization. Participants will be informed that they are enrolled in 1 of 3 groups, that all groups receive high-value, individualized care, and that the number and frequency of follow-up sessions may vary. However, they will not be told whether they are assigned to a stepped care, usual rehabilitation care, or usual medical care, thereby maintaining partial blinding regarding group allocation. They will only be informed about the interventions received by participants in the other groups after completing the 24-week follow-up. To minimize potential contamination, each group will receive treatment in separate clinics: Usual medical care in medical clinics, while stepped care and usual rehabilitation care will be provided in different physiotherapy clinics. Co-interventions will be monitored at each follow-up using a questionnaire on REDCap.

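### The primary mixed model, as described, gives the stratification factors only an interaction-test role, names no baseline covariate and relies on one participant random effect; adjustment and a freer covariance would improve the week-24 interval at no cost

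*Protocol article*

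**What the plan says.** The Statistical Analysis Plan section of the protocol article specifies "linear mixed models with a random effect by participant to account for the correlation present in repeated measures within individuals". The fixed effects it names are group, time and their interaction. Residuals are to be checked for normality and constant variance, with a generalized linear mixed model as the fallback. Effect sizes are to be expressed as standardized between-group differences in average improvement per week over 12 and 24 weeks.

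Under Randomization and Blinding, "randomization was stratified by gender (men, women, and other) and MSKD", which produced 12 lists. In the analysis these two factors have one stated role: "Gender and type of MSKD will be used to test the interaction between the group effect and the strata".

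The primary outcome is BPI-SF Pain Interference at 24 weeks. It is also measured at baseline, 6 and 12 weeks. No baseline covariate is named, and the text does not say whether the baseline score enters as a covariate or as one of the repeated responses.

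**The concern.** Three features of the described model fall short of what the collected data allow.

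- **Strata.** Factors chosen for stratification are normally expected to be prognostic. A model without their main effects leaves the variance they explain in the error term.
- **Baseline.** The baseline value of the same scale is usually among the strongest predictors of the week-24 score. Leaving it out, or using it only through a change score, widens the interval.
- **Covariance.** A single participant random effect is most naturally read as a random intercept, which imposes equal variances at all visits and equal correlations between all pairs of visits. Correlations between visits 24 weeks apart are often weaker than between adjacent visits. The residual checks named would not reveal that, and the named fallback would not address it.

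At stake are the width and the coverage of the confidence interval on which noninferiority is judged. An SE that is too small is the harmful direction in a noninferiority trial.

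**Working it through.** **Inputs from the protocol article** (sample-size paragraph at the end of the Anterior Knee Pain subsection): "using a noninferiority margin of 2.0 (out of 10) points on the primary outcome measure"; "an SD of 1.8 in the usual care groups"; "The sample size calculation assumes a true mean difference of 0 between groups"; "a 1-sided alpha level of .025"; "a 15% dropout rate at the 24-week follow-up"; 123 per group for 80% power. Evaluable per arm: 123 × 0.85 = 104.55, taken as 104.

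**Assumed inputs:** all correlations, visit-specific SDs and the share of variance explained by the strata. The article gives none, so ranges are shown.

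**The plan's own figure.** n = 2 × [1.8 × (1.960 + 0.842) / 2.0]² = 12.7, so 13 evaluable per group, and 13 / 0.85 = 15.3, so 16 enrolled. The stated 123 is not reproduced. A margin of 0.7 does reproduce it (104 evaluable; 104 / 0.85 = 122.4, so 123), but the article does not state that margin. This mismatch is a separate matter. It is needed here only to judge what precision is worth.

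**Step 1, baseline adjustment.** With ρ the baseline-to-week-24 correlation:

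- unadjusted SE = 1.8 × √(2/104) = 0.250
- change-score SE = 0.250 × √(2(1 − ρ))
- baseline-adjusted SE = 0.250 × √(1 − ρ²)

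| ρ | Unadjusted | Change score | Adjusted | Narrower than unadjusted | Narrower than change |
|---|---|---|---|---|---|
| 0.3 | 0.250 | 0.295 | 0.238 | 5% | 19% |
| 0.5 | 0.250 | 0.250 | 0.216 | 13% | 13% |
| 0.7 | 0.250 | 0.193 | 0.178 | 29% | 8% |

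**Step 2, strata main effects.** The SE is multiplied by √(1 − R²). For R² of 2%, 5%, 10% and 15% the factors are 0.990, 0.975, 0.949 and 0.922, a reduction of about 1% to 8%.

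**Step 3, random-intercept covariance, change from baseline to week 24.** With constant SD and complete data, the model replaces the week 0-24 correlation by the average over all pairs of visits. Model SE / true SE = √[(1 − average ρ) / (1 − ρ for weeks 0-24)].

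- Equal correlations: ratio 1.00.
- Correlations 0.6 (weeks 0-6), 0.5 (0-12), 0.4 (0-24), 0.7 (6-12), 0.55 (6-24), 0.7 (12-24): average 0.575. Model SE = 1.8 × √[(2/104) × 2 × 0.425] = 0.230; true SE = 1.8 × √[(2/104) × 2 × 0.6] = 0.273; ratio 0.84. One-sided error at the margin is Φ(−1.96 × 0.842), about 5% instead of 2.5%.
- Milder decay, 0.7 × 0.85^(weeks/6): average 0.50, weeks 0-24 0.37; 0.250 against 0.281, ratio 0.89. One-sided error about 4.1%.
- Milder decay, 0.6 × 0.8^(weeks/6): average 0.38, weeks 0-24 0.25; 0.278 against 0.307, ratio 0.91. One-sided error about 3.8%.

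Adding rising or falling SDs to the two milder patterns keeps the ratio at 0.88 to 0.91. Across all the decay scenarios the SE is therefore about 9-16% too small.

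**Step 4, random-intercept covariance, week-24 mean difference.** The model uses the average of the four visit variances.

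- SD 1.8 throughout: ratio 1.00, whatever the correlations.
- SDs 1.5, 1.8, 1.9, 2.1: average variance 3.378 against 4.41 at week 24; 0.255 against 0.291, ratio 0.88.
- SDs 2.1, 2.0, 1.9, 1.8: average variance 3.815 against 3.24; 0.271 against 0.250, ratio 1.09.

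**Step 5, does it change a decision?** Power = Φ(margin / SE − 1.96). At margin 2.0, even the largest SE met in these scenarios (0.334, change score with falling SDs) gives Φ(5.99 − 1.96), above 99.99%. At a margin of 0.7, power for ρ from 0.3 to 0.7 would be about 66-95% on change scores, 80% unadjusted and 84-97.5% baseline-adjusted.

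**The case against.** The article condenses a fuller plan, and residual covariance, covariate lists and baseline handling are often left to that plan. A random effect by participant does not rule out a further residual structure. A standard model for a group-by-stratum interaction would contain the strata main effects. A response vector that includes baseline with a common baseline mean would recover most of the baseline precision, and the text does not exclude it. Leaving strata out after stratified randomization generally makes inference conservative, not invalid.

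Much of this stands, and it rules out three stronger readings that a reader might infer.

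- **That the model handles baseline as a repeated response.** This is suggested by effect sizes expressed as weekly improvement, but that sentence governs presentation. The article does not say how baseline enters the model.
- **That the 24-week SE is misstated.** At constant SD the week-24 difference has the correct SE. With unequal SDs the error may go either way.
- **That the false noninferiority rate doubles to 5%.** That figure belongs to the change contrast under one assumed correlation pattern. Milder decay gives about 4%, and equal correlations and variances give no inflation.

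The objection does not dispose of the point. The section is not silent: it sets out the model terms, the random effect and the role of the strata, and that role is interaction testing only. Suggesting a better model than the one described is different from complaining of missing detail.

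**Conclusion.** The point holds as a worthwhile improvement in precision and in robustness to the covariance assumption. It is not a demonstrated error in the 24-week standard error. At SD 1.8 and 104 evaluable per arm, baseline adjustment is worth about 5-29% of the SE against an unadjusted contrast, or 8-19% against a change score, for an assumed correlation of 0.3 to 0.7. Strata main effects add about 1-8% for an assumed 2-15% of variance explained. The random-intercept SE ranges from correct to about 16% too small for change from baseline. For the week-24 difference it ranges from about 12% too small to 9% too large. These sizes rest on correlations and variances that the article does not give.

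Power at the stated margin of 2.0 is unaffected. The benefit is a narrower interval with sound coverage, and it would bear on the decision only if the margin actually applied were much smaller than 2.0.

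**What to change.** For the week-24 noninferiority contrast, specify one repeated-measures model with:

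- group, visit and group-by-visit;
- main effects of gender and MSKD type, pooling the 'other' gender level if it is too sparse to estimate;
- baseline BPI-SF Pain Interference, either as a covariate or as a response with baseline means constrained equal across arms;
- an unstructured covariance over visits, with small-sample degrees of freedom.

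Keep the group-by-gender and group-by-MSKD tests as exploratory analyses outside the primary model.

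The cost is wording only. All variables are already collected. An unstructured covariance has 6 parameters for three visits or 10 for four, which 369 participants support easily. Recruitment is continuing and no interim analysis is planned, so the change can be made before any outcome comparison.

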### Mitigation Plan

As with any clinical trial, maintaining adherence to the intervention and follow-ups may be challenging for some participants. To encourage compliance, several strategies will be implemented. Medical and rehabilitation interventions will be held in clinics offering both daytime and evening appointment options. Follow-up assessments will be conducted online to minimize travel requirements. Automated reminders will be sent via email as needed, and research associates will be available to provide assistance via email or phone. In addition, participants will receive CAD $40 (approximately US $28.50 as of October 2025) at the baseline evaluation to cover travel expenses and another CAD $40 (approximately US $28.50 as of October 2025) at the end of the project to compensate for time spent completing follow-up questionnaires.

### Ethical Considerations

Ethics approval has been granted by the Comité d’éthique de la recherche sectoriel en réadaptation et intégration sociale du CIUSSS de la Capitale-Nationale (Rehabilitation and Social Integration section; #2024-2982). All participants will receive a comprehensive information and consent form outlining the nature and objectives of the study.

Participation is entirely voluntary. Participants may decline to take part or withdraw from the study at any time, without providing a reason, by informing the principal investigator or a member of the project staff. They may also request that any data collected from them be withdrawn.

Electronic informed consent will be required before enrollment. Participants’ confidentiality will be maintained by the research team throughout the project in accordance with current regulations. Participants’ identities will be coded, and all data will be stored in secure folders within the research team’s offices or in password-protected files. It will not be possible to identify participants in any publications.

### Patient and Public Involvement

The website used during the first six weeks of the stepped care intervention was co-created with seven patient-partners living with chronic MSKDs (mean age 49.4 y, SD 14.7 y; 71% women). The website underwent iterative development until it received approval from the patient-partners. They also provided feedback on the selected set of patient-reported outcome measures to ensure that the completion burden was acceptable and that all important constructs were adequately assessed. Additionally, a patient partner contributed to the design of the study protocol to ensure its relevance and alignment with patient needs.

## Results

The Edu-First trial is funded by a project grant from the Canadian Institutes of Health Research (grant #495615), with funding spanning from October 2023 to September 2028.

Recruitment began on January 31, 2025, with the first participants enrolled in February 2025. As of September 2025, a total of 65 participants have been enrolled. Recruitment is expected to continue for up to 3 years, aiming for approximately 10 new participants per month, and is anticipated to be completed by Winter 2028. Data analysis and manuscript preparation are projected to take up to 6 months, with the first manuscripts anticipated for submission by Fall 2028.

## Discussion

### Principal Findings

We anticipate that the stepped care model will be noninferior to usual medical care and usual rehabilitation care in terms of treatment effectiveness. In addition, we expect this model to reduce health care costs by limiting the use of expensive resources, such as consultations with health care providers and medical investigations. As health care costs for MSKDs continue to rise, implementing a stepped care model—where patient education and self-management advice are prioritized initially, and usual care is reserved for those whose symptoms persist—could improve access to care without compromising quality. This approach also empowers patients to take an active role in managing their condition, overall health, and well-being from the outset.

MSKDs are among the most common reasons for primary care consultations, with up to 20% of adults seeking care for these conditions annually [8], and approximately 30%-40% of individuals with MSKDs reporting contacting their family physician for these complaints [30]. Despite their high prevalence, MSKDs remain difficult to treat effectively beyond the acute phase [96-98]. Given the significant impact of MSKDs on individuals’ activities and participation, as well as their contribution to societal burdens such as work loss, disability pensions, early retirement, and increased demand for social support [3,4], it is crucial to explore innovative care models to address these challenges.

The findings from this study could inform systemic changes in care delivery, improving access to treatment while reducing the average cost per care episode. Ultimately, this study aims to provide robust evidence supporting more efficient, patient-centered care models for a prevalent and costly set of conditions.

### Strengths and Limitations

This study is designed as a pragmatic randomized controlled trial, reflecting real-world clinical practice and enhancing the generalizability of its findings. Key strengths include the direct comparison of the stepped care model with 2 of the most widely used care models, the inclusion of cost-effectiveness analyses, and the focus on patient-centered outcomes. Potential limitations include the reliance on patient-reported data for some outcomes, which may introduce reporting bias, and the heterogeneity of MSKD presentations, which could influence treatment response. In addition, given the pragmatic nature of the trial, variability in usual care practices may impact the consistency of comparator interventions.

### Future Directions

If the stepped care model proves to be noninferior in effectiveness and superior in cost-effectiveness, the results could guide systemic improvements in the delivery of MSKD care. Wider implementation of this model may improve access to health care services, particularly in primary care settings, while reducing the economic burden on both patients and the health care system. Future research could explore long-term outcomes, patient adherence to self-management strategies, and the applicability of this model to other musculoskeletal conditions or health care systems.

### Dissemination Plan

At the conclusion of the project, targeted materials will be developed for patients, clinicians, managers, and decision-makers. These will include infographics, podcasts, webinars, presentations, and videos, which will be shared through a variety of clinical and community platforms, including the websites and social media channels of professional associations and key partners. Academic dissemination will include peer-reviewed manuscripts and conference presentations to ensure broad visibility within the scientific community.

## Appendix

Multimedia Appendix 1 Recruitment process.

Multimedia Appendix 2 Peer-review report by the Project. Grant / Subvention Projet - Clinical Investigation - B 2 / Investigation clinique B 2 - Canadian Institutes of Health Research (CIHR) / Instituts de recherche en santé du Canada (IRSC).

## Abbreviations

BPI-SF: Brief Pain Inventory – Short Form
CoPaQ: Cost for Patients Questionnaire
CONSORT: Consolidated Standards of Reporting Trials
CSI: Central Sensitization Inventory
HADS: Hospital Anxiety and Depression Scale
HRQoL: health-related quality of life
ICER: incremental cost-effectiveness ratio
KOS-ADLS: Knee Outcome Survey Activities of Daily Living Scale
MSKD: musculoskeletal disorder
NDI: Neck Disability Index
ODI: modified Oswestry Disability Index
ÖMPQ: OREBRO musculoskeletal pain questionnaire
PCS: Pain Catastrophizing Scale
PSEQ: Pain Self-Efficacy Questionnaire
QuickDASH: shortened version of the Disabilities of the Arm, Shoulder, and Hand
REDCap: Research Electronic Data Capture
SPIRIT: Standard Protocol Items: Recommendations for Interventional Trials
TIDieR: Template for Intervention Description and Replication
TSK: Tampa Scale of Kinesiophobia
